### Interim analysis {21b}

An interim analysis, methodically embedded within the study protocol, serves as an evaluation of the foundational assumptions underpinning the original design and sample size calculations. The objectives of the interim analysis extend beyond the purview of methodological scrutiny. They encompass the imperative need to inform decisions regarding the continuation of the (UM) patent of roflumilast (US20150051254A1), specifically focusing on its application in the treatment of cognitive impairment. This juncture underscores the translational impact of the study, linking scientific exploration with potential intellectual property considerations.

The execution of the interim analysis necessitates unblinded access to treatment group assignments. This pivotal task will be entrusted to an impartial and independent researcher possessing specialized expertise in repeated measure design. The timing of this interim is aligned with the enrollment trajectory, with the analysis slated to transpire precisely after half of the predetermined total participant cohort have fulfilled their participation commitment.

### Methods for additional analyses (e.g. subgroup analyses) {20b}

Subgroups are defined based on baseline characteristics including sex, age, and education. We will investigate the effect of age in a stratified manner. By stratifying the groups into two age categories, e.g. < 70 and > 70, as well as stratifying the groups in two education categories, i.e. low and high education.

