### Eligibility criteria {10}

To be eligible to participate in this study, prospective participants must meet the following eligibility criteria: age within the range of 50 and 90 years, willingness and capability of both the participant and (informal) caregiver, to provide and sign informed consent. Additional criteria include a body mass index (BMI) between 18.5 and 35, an MMSE total score of 20 or higher, and a clinical diagnosis of aMCI or mild dementia (probable AD) diagnosis, which entails a memory performance on the delayed recall of the 15-VLT of one or more standard deviation(s) below the normative score, corrected for age, education, and sex. Furthermore, a global clinical dementia rating (CDR) scale total score of 0.5 or 1. Mild dementia (probable AD) is defined according to the Clinical Core Criteria of McKahn in 1987, updated in 2011 [23].

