### Sample size {14}

Following a previous study demonstrating an estimated effect size of 0.69 (Cohen’s *d*) in healthy elderly and individuals with pronounced age-associated memory impairment [16], a power calculation for *F*-tests has been performed. This results in group sizes of 24 participants per group (Power 0.8; alpha 0.05), in consideration of potential dropout rates observed in the previous study, wherein nearly 10% of the participants withdrew for reasons unrelated to drug effects. To mitigate potential attrition, an additional 3 participants per treatment group will be included, resulting in 27 participants per group.

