### Statistical methods

#### Statistical methods for primary and secondary outcomes {20a}

Descriptive statistics for continuous parameters will include sample sizes, means and standard errors of the dependent variables, and covariates for each distinct level combination of factors. For categorical data, summary tables will present counts and percentages. Statistical summaries will be presented by treatment, sequence, or period. The repeated measures, namely the outcome variables of the cognitive assessments and the subjective well-being-related scales, will be analysed using mixed models. The between-subject factor will be the treatment group (three levels: placebo, 50 μg roflumilast, and 100 μg roflumilast). The scores of each task will be entered as the within-subject factor, as well as time (T1, i.e. acute, T2, i.e. 12 weeks, T3, i.e. 24 weeks, T4, i.e. 2-week follow-up). An additional interaction term between the treatment group and time is included to determine whether the different treatment groups will lead to different trajectories over time. Subject covariates included will be sex, age, and education. Additionally, at the end of the study, we will ask each participant which intervention arm they think they have received (placebo, 50 mcg roflumilast, or 100 mcg roflumilast). Because of exclusion and inclusion criteria related to the patient recruitment of the study, the population recruited will be homogenous. Note that groups will not be able to be matched because of the applied randomization block strategy. The significance level will be set at *a* = 0.05.

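### The stated subgroup analyses only stratify by age and education, so they do not test whether the treatment effect differs by either, and the example age cut places nobody aged 70

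*Protocol article*

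**What the plan says.** All references are to the protocol article.

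- **Methods for additional analyses {20b}.** Subgroups are to be defined by sex, age and education. For age, the text says "We will investigate the effect of age in a stratified manner". The categories follow as "By stratifying the groups into two age categories, e.g. < 70 and > 70", and for education as "stratifying the groups in two education categories, i.e. low and high education". No analysis by sex is described beyond its being listed.
- **Statistical methods for primary and secondary outcomes {20a}.** Age and education enter the mixed model as adjustment terms: "Subject covariates included will be sex, age, and education". The only interaction mentioned is with time: "An additional interaction term between the treatment group and time is included".
- **Eligibility criteria {10}.** Entry requires "age within the range of 50 and 90 years", so age 70 is eligible.
- **Sample size {14}.** Planning starts from "a previous study demonstrating an estimated effect size of 0.69" (Cohen's d) and arrives at "group sizes of 24 participants per group (Power 0.8; alpha 0.05"), raised to 27 per group for dropout.

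**The concern.** Whether a treatment works differently in younger and older participants is a question about the difference between two treatment effects. A covariate main effect for age does not answer it, because it adjusts outcome levels for age and leaves the treatment effect common to all ages. Results shown by stratum do not answer it either, because each describes one stratum and neither estimates the difference between them. Taken together, the two statistical sections name no term that does.

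The stake is interpretive. With small strata, one can easily reach significance while the other does not, even when the true effect is the same in both. A reader could take that pattern to mean the drug helps only one age or education group. The same opportunity arises for age and for education, and for each active dose against placebo.

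The age categories add a smaller problem: read literally, they are not exhaustive.

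**Working it through.** **Plan's own figures.** The plan gives no figure for the subgroup analyses. Its sample size is used here only to size the strata. The dropout step reproduces: 24 / (1 − 0.10) = 26.7, rounded up to 27. The starting figure of 24 depends on inputs the text does not state, and it is not at issue here.

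**1. Who falls in the gap at 70.** Inputs: 81 participants (3 × 27) and eligible ages 50 to 90. The age distribution is not given, so it is assumed, with age taken in completed years.
- Uniform over the 41 single years: 81 / 41 = 2.0 participants.
- Normal, mean 68 to 75 and SD 6 to 10: 81 × [Φ((71 − mean)/SD) − Φ((70 − mean)/SD)] runs from 2.9 (mean 75, SD 10) to 5.4 (mean 70, SD 6). At mean 70 and SD 8 it is 4.0.

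This gives about 2 to 5 of 81. If exact age from date of birth were used, almost nobody would be at exactly 70.0 and the loss would be about zero.

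**2. Power within a stratum.** Assumptions: an even split of 24 to 27 per arm, hence about 12 to 13 per arm per stratum; one active arm against placebo; a simple two-sided t-test at 0.05; d = 0.69.
- Noncentrality = d × √(n/2). For n = 13 it is 0.69 × √6.5 = 1.76 on 24 degrees of freedom, which gives power 0.393.
- For n = 12 it is 0.69 × √6 = 1.69 on 22 degrees of freedom, which gives power 0.366.

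**3. Chance that exactly one of two strata is significant when the true effect is the same in both.** For independent strata this is 2p(1 − p), where p is the power within a stratum.
- n = 13: 2 × 0.393 × 0.607 = 0.477.
- n = 12: 2 × 0.366 × 0.634 = 0.464.

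The result depends on the true effect. At 13 per arm per stratum:

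| True d in both strata | Power in each stratum | Exactly one significant |
|---|---|---|
| 0.69 | 0.39 | 0.48 |
| 0.5 | 0.23 | 0.36 |
| 0.4 | 0.17 | 0.28 |
| 0.3 | 0.11 | 0.20 |
| 0 | 0.05 | 0.095 |

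A valid interaction test at the 5% level would give a false signal about 5% of the time in every row.

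**4. What a direct contrast could detect.** The treatment-by-stratum contrast for one active arm against placebo has standard error SD × √(4/n), with n per arm per stratum. Power for a between-strata difference of 0.69 SD is approximately Φ(0.69/SE − 1.96).
- n = 12: SE = 0.577; Φ(1.195 − 1.96) = 0.22. The difference detectable with 80% power is 2.80 × 0.577 = 1.62 SD.
- n = 13.5: SE = 0.544; Φ(1.268 − 1.96) = 0.24. The detectable difference is 2.80 × 0.544 = 1.52 SD.

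**The case against.** The strongest reply is that this reads too much into a short paragraph. The age cut is introduced as an example, so its boundary may be a slip that the full protocol or analysis plan corrects. Nothing says that separate models will be fitted, since stratifying could mean a stratum factor in the planned mixed model. Nothing says that significance in one stratum and not the other will count as evidence of a differing effect. The 48% holds only near d = 0.69, with an even split and a plain t-test, whereas the plan is a covariate-adjusted repeated-measures model. The proposed replacement is itself weak at this sample size.

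Most of that stands and limits the point. A reader might infer that 70-year-olds are definitely excluded, that the trial will make subgroup claims from split significance verdicts, or that conflicting verdicts would arise half the time whatever the true effect. The documents support none of these. The cut is illustrative, no such decision rule is written, and the probability falls to about 10% when there is no effect.

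What does not stand is the suggestion that this is only missing detail. The article does choose a method for these subgroups, and that method, together with the covariate role of the same variables, does not address effect modification. Leaving the cut as an example also leaves it open to choice after the data are seen. Low power for an interaction is a reason to show the estimate with its interval, because two separate verdicts hide that uncertainty.

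**Conclusion.** The point holds in a limited form and is minor. As stated, the analyses by age and education do not test whether the treatment effect differs by either variable, and the example age categories are not exhaustive.

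The gap at 70 concerns about 2 to 5 of 81 participants, on assumed age distributions and age in completed years; alone it would be close to clerical. The risk of a misleading contrast between strata is conditional on stratum results being read as evidence of a differing effect. On that condition it is about 46% to 48% at the planning effect, for an even split and a simple two-sided t-test, and less for smaller effects. The primary analysis is untouched, and an analysis plan that is not shown may already add the missing test.

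**What to change.** In the section on additional analyses:

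- Add treatment-by-age and treatment-by-education contrasts at week 24 to the mixed model already planned, preferably with age continuous.
- Report each as an estimate with a 95% confidence interval, and label the analyses exploratory.
- If age groups are displayed, make them exhaustive and fix them in advance, for example < 70 and ≥ 70.

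This is a change of analysis wording with slightly more analysis work; it needs no new data, visits or participants. Continuous age brings a linearity assumption. Power for a between-strata difference of 0.69 SD remains only about 22% to 24%, so a non-significant interaction should not be read as showing equal effects.

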### Methods in analysis to handle protocol non-adherence and any statistical methods to handle missing data {20c}

Advantages of LMM over ANOVA-based repeated measures include that it does not use listwise deletion, as it handles missing observations by using maximum likelihood to estimate missing values conditional on covariates [51].

### Plans to give access to the full protocol, participant-level data and statistical code {31c}

The full protocol, anonymized data set, and statistical code will be available on request after the results of the study have been published.

## Oversight and monitoring

### Composition of the coordinating centre and trial steering committee {5d}

***User committee (yearly meetings)***

(research team, representative ZonMw, representative Alzheimer Nederland, representative Hersenstichting, representative client panel Alzheimer Centrum Limburg, health technology assessment officer, business developer, project advisor, and health economist).Provide inputMonitor progressDiscuss bottlenecksDiscuss/improve participation and dissemination plan follow-up process to embed the innovation into healthcare

### Composition of the data monitoring committee its role, and reporting structure {21a}

No data monitoring committee DMC was appointed for this trial as this study is classified as a medium risk by the local Medical Research Ethics Committee (MREC), a low burden, and a single-centre study.

### Adverse event reporting and harms {22}

All AEs reported spontaneously by the participant or observed by the investigator or his staff will be recorded. All AEs will be monitored until they have abated, or until a stable situation has been reached. Depending on the event, follow-up may require additional tests or medical procedures as indicated, and/or referral to the general physician or a medical specialist. SAEs need to be reported till the end of the study within the Netherlands, as defined in the protocol. All SAEs will be reported through the web portal ToetsingOnline to the accredited MREC that approved the protocol, within 7 days of first knowledge for SAEs that result in death or are life-threatening followed by a period of maximum 8 days to complete the initial preliminary report. All other SAEs will be reported within a period of a maximum of 15 days after the research team has first knowledge of the SAEs. SAEs that result in death or are life-threatening should be reported expedited. The expedited reporting will occur not later than 7 days after the responsible investigator has first knowledge of the adverse reaction (AR). This is for a preliminary report with another 8 days for completion of the report. Suspected unexpected serious adverse reactions (SUSARs) will be reported through the web portal ToetsingOnline to the MREC: SUSARs that have arisen in the clinical trial that was assessed by the MREC; or SUSARs that have arisen in other clinical trials of the same sponsor and with the same medicinal product, and that could have consequences for the safety of the subjects involved in the clinical trial that was assessed by the MREC.

The remaining SUSARs are recorded in an overview list (line-listing) that will be submitted once every 6 months to the MREC. This line-listing provides an overview of all SUSARs from the study medication, accompanied by a brief report highlighting the main points of concern. The expedited reporting of SUSARs through the web portal Eudravigilance or ToetsingOnline is sufficient as a notification to the competent authority. The investigator will report expedited all SUSARs to the competent authorities in the other Member States, according to the requirements of the Member States. The expedited reporting will occur not later than 15 days after the sponsor has first knowledge of the ARs. For fatal or life-threatening cases, the term will be a maximum of 7 days for a preliminary report with another 8 days for completion of the report. One of the senior researchers not involved in subject testing or data analysis will reveal the individual subject code. The subject will be excluded from the study.

In addition to the expedited reporting of SUSARs, the investigator will submit, once a year throughout the clinical trial, a safety report to the accredited MREC, competent authority, and competent authorities of the concerned Member States. The annual safety report will be combined with the annual progress report. The safety report consists of a list of all suspected (unexpected or expected) SARs, along with an aggregated summary table of all reported SAEs, ordered by organ system, per study, and a report concerning the safety of the subjects, consisting of a complete safety analysis and an evaluation of the balance between the efficacy and the harmfulness of the medicine under investigation.

Potential side effects attributable to the investigational study drug, roflumilast, are reported in the form of the Daxas package leaflet in the patient information sheet. These side effects, extrapolated from the known outcomes associated with the administration of 250 µg and 500 µg roflumilast dosages, serve as a critical informational resource for study participants. Importantly, the informational transparency is accompanied by a candid acknowledgement of the uncertainty regarding the applicability of known side effects to the lower dosages employed in this study, specifically the 50- and 100-µg variants. Acknowledging the nuanced nature of pharmaceutical interventions, the patient information sheet explicitly underscores the proactive surveillance mechanisms instituted to inquire about participants’ emotional and physical well-being. A stringent regimen of regular telephonic engagement has been instituted, empowering participants to promptly communicate any perceived side effects. Additionally, a perpetual availability of a qualified research physician ensures real-time responsiveness to participant inquiries, further amplifying the vigilance inherent in this study. To bolster the ongoing safety evaluation, an iterative process of annual updates to the development safety update report is rigorously adhered to. These updates are dutifully submitted to the evaluation of the MREC.

### Frequency and plans for auditing trial conduct {23}

As this trial falls under the scope of the Dutch Medical Research Involving Human Subjects Act (Dutch: Wet Medisch-Wetenschappelijk Onderzoek Met Mensen; WMO), the CTCM has appointed an independent clinical research monitor to oversee the study. The designated individual monitors whether the study is conducted according to the ICH-GCP guidelines, legislation, and regulations. Collaboratively with the research team, a comprehensive monitoring plan is prepared, in which all details regarding the procedures are stated. This plan is made according to the specific demands of the study and in line with legislation and regulations. The expertise offered by CTCM extends beyond mere monitoring, encompassing advisory roles on intricate matters related to laws and regulations. CTCM, in its oversight capacity, conducts a review of data collection processes, verifying source documents and eCRFs. This review extends to inspecting Informed Consent forms and protocols, ensuring their alignment with regulatory standards. Moreover, CTCM undertakes a vigilant examination of reports pertaining to AEs and complications.

### Plans for communicating important protocol amendments to relevant parties (e.g. trial participants, ethical committees) {25}

Amendments are changes made to the research after approval of the study protocol by the accredited MREC. All amendments will be notified to the MREC that approves the protocol gives a favourable opinion. A “substantial amendment” is defined as an amendment to the terms of the MREC application, or to the protocol or any other supporting documentation, that is likely to affect to a significant degree such as the safety or physical or mental integrity of the subjects of the trial, the scientific value of the trial, the conduct or management of the trial, or the quality or safety of any intervention used in the trial. All substantial amendments will be notified to the MREC and the competent authority. Nonsubstantial amendments do not have to be notified to the accredited MREC and the competent authority but will be recorded and filed by the investigator. If significant amendments are made, participants will be informed and asked to sign a new informed adapted consent. In case of significant amendment, trial registries will be updated.

### Dissemination plans {31a}

All results from this research will be disclosed unreservedly in a scientific paper aimed for publication in a peer-reviewed scientific journal. The list of authors will include all individuals who made substantial contributions to the conception and design, or analysis and interpretation of data, as well as drafting the paper or revising it for important intellectual content. Publication is not restricted or limited in any way by the actual outcome of the study. All results, both negative and positive, will be incorporated in the paper. In addition, the results will be presented at one or more national and/or international scientific conferences either as posters or oral presentations. The participant’s data will not be disclosed to unauthorized third parties, and participant confidentiality will always be maintained. Publication takes place in accordance with the rules in the CCMO statement publication policy.

## Discussion

Building upon our department’s previous investigations involving pronounced age-associated memory impaired/amnestic MCI participants, a prospective delay of 3–5 years in the conversion from MCI to dementia is anticipated [21]. This potential delay holds significant promise, potentially deferring nursing home admissions and thus substantial cost reduction spent on the care of patients diagnosed. Even in cases of eventual conversion, the anticipated benefits of roflumilast, such as cognitive stabilization and neuroprotective effects, are presumed to persist in AD patients. This underscores the potential longevity of positive outcomes, given the average life expectancy of AD dementia patients. In essence, the envisioned efficacy in aspects of daily living has profound implications for cost reduction in care and related expenses.

The investigational utilization of roflumilast, a registered medicinal product, brings forth a consideration of potential AEs and their implication in the context of cognitive function. Our evaluation, drawn from prior studies from our department, predicates that reported AEs are predominantly mild and transient, resolving within 24 h post-intake, even at doses surpassing those tested in the current study. The potential positive outcomes, specifically enhanced or stabilization of cognitive function, neuroprotective effects, and the prospective delay of mild or moderate AD dementia, are strategically weighed against the backdrop of the most prevalent side effects associated with roflumilast. Crucially, the absence of established pharmacological treatments for patients with MCI in Europe underscores the pioneering nature of our study. The study cohort, comprising (geriatric) participants aged 50 to 90, exhibits a lack of specific susceptibilities to roflumilast, reinforcing the scientific rationale for exploration.

To enhance participant safety, a proactive risk reduction approach is instituted, involving regular researcher-patient interactions. A structured communication cadence, including weekly contacts during the initial month and bi-weekly engagements in subsequent months, facilitates the timely documentation of side effects and patient concerns. Weight loss, identified as a common side effect, is vigilantly monitored through weight measurements on each test day. Exclusion criteria, incorporating a BMI threshold of under 18.5, further contribute to refining participant selection and ensuring their well-being.

Access to the Electronic Patient File provides a real-time conduit for the principal investigator and co-investigator to investigate AEs and SAEs for Maastricht University Medical Centre + (MUMC +) participants. This pre-emptive measure empowers the research team with valuable insights before each test day, fostering a proactive stance in ensuring participant safety. Evidence from clinical studies indicates that the majority of patients, post-treatment discontinuation, regain lost weight, allaying concerns related to this common side effect. Importantly, the comprehensive review of clinical studies reveals an absence of reported overdose cases with roflumilast, reinforcing its favourable safety profile.

Finally, the adaptation of exclusion criteria, meticulously tailored to exclude clinical participants at heightened risk of side effects or with diminished therapeutic responsiveness to roflumilast, further exemplifies the study’s commitment to participant safety. In summary, this scientific justification underpins the study’s robust risk mitigation strategies, positioning the investigation of roflumilast for cognitive enhancement as a pioneering and conscientiously conducted endeavor in the realm of pharmacological interventions for cognitive function.

